### Sample size calculation

For the determination of sample size, we used G*power [32]. Since no study so far tried to downregulate hippocampal activity, we opted for the detection of at least a small effect (i.e., cohen’s *f* = 0.25). This would require an inclusion of *n* = 84 in total (that is, *n* = 21 in each group) for a repeated measures design with 4 groups and 4 measurements (i.e., baseline, post-intervention, follow-up 1, follow-up 2). We used the following criteria to calculate sample size: ANOVA with repeated measurements and between-within interactions, α err = 0.01, 1-β = 0.99, number of groups = 4, number of measurements = 4.

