### Follow-up assessments

Approximately 6 and 12 months after the intervention, we will implement follow-up assessments. At the 6-months follow-up, we will only acquire behavioural data with the VLMT. At 12-months follow-up, we will apply the VLMT, draw blood again to obtain amyloid levels, and apply structural as well as functional MRI. For the fMRI task, we will again examine pattern separation performance (with different objects). In addition, participants will be examined using the MoCA (in healthy controls) or the CFD (in patients with MCI) for a second time.

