### Statistical analyses

The primary outcome is the change in hippocampal activity as assessed with a pattern separation task during fMRI before and after both neurofeedback sessions. For the determination of intervention effects on hippocampal activity, we will compute repeated measures ANOVA with intervention (experimental vs. control group) and group (healthy volunteers vs. patients with MCI due to AD) as between-subject factors. We will include the genetic variants of ApoE and BDNF as covariates. Next, we are planning to compute regression analyses since we hypothesize that the reduction of hippocampal activity will be associated with memory performance change in the pattern separation task and the VLMT. As exploratory analyses, we will investigate whether any variable predicts successful neurofeedback; we will calculate the association between Aβ levels in blood and hippocampal activity; and we will identify the most successful downregulation strategies. For the prediction of successful neurofeedback, we will apply machine learning methods (e.g., cross-validated non-linear multivariate classification) to obtain the most important features.

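### The stated 99% power is calculated for four measurements, but the fMRI primary outcome is a two-point change and fMRI is scheduled at only three visits

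*Protocol article*

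**What the plan says.** In the Protocol article, Sample size calculation gives the test as "ANOVA with repeated measurements and between-within interactions", the error rates as "α err = 0.01, 1-β = 0.99" and the dimensions as "number of groups = 4, number of measurements = 4", with an effect size of Cohen's f = 0.25. It describes the layout as a "repeated measures design with 4 groups and 4 measurements (i.e., baseline, post-intervention, follow-up 1, follow-up 2") and arrives at 84 participants, 21 in each of four cells (two interventions by two diagnostic groups).

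Three other places describe the outcome being sized:

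- **Statistical analyses** defines that outcome in one sentence: "The primary outcome is the change in hippocampal activity as assessed with a pattern separation task during fMRI before and after both neurofeedback sessions". That is two time points. The analysis is a repeated measures ANOVA with intervention and diagnostic group as between-subject factors. The text does not say which interaction with time is decisive.
- **Follow-up assessments** limits the 6-month visit: "At the 6-months follow-up, we will only acquire behavioural data with the VLMT". Functional MRI is repeated at 12 months.
- **Table 1 (Study procedure):** functional MRI is marked at Baseline II, Post-Intervention and Follow-up II, and nowhere else.

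**The concern.** Hippocampal activity cannot have four measurements under this schedule, because one of the four named visits has no scan. Of the outcomes named in the analysis, only the verbal learning test (VLMT) is collected at all four of those visits, and it is not primary. The calculation is motivated by downregulation of hippocampal activity, so it was not meant for the VLMT.

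The number of measurements matters because, in the standard calculation for a within-between interaction, the noncentrality parameter is proportional to it. Counting four where the outcome has two doubles that parameter. At stake is the accuracy of the only justification given for N = 84, and of the 1% type II error that a reader would apply to a null primary result.

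**Working it through.** **Inputs from Sample size calculation:** f = 0.25, alpha = 0.01, target power 0.99, k = 4 groups, m = 4 measurements, N = 84.

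**Inputs assumed:** correlation among measurements rho and non-sphericity epsilon are not given. I take rho = 0.5 and epsilon = 1, then vary rho from 0.3 to 0.7. No dropout is applied.

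**Formula (noncentral F, within-between interaction, epsilon = 1):**

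- lambda = f² × N × m / (1 − rho)
- df1 = (k − 1)(m − 1)
- df2 = (N − k)(m − 1)
- power = P(F′(df1, df2, lambda) > F critical at alpha = 0.01)

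**Step 1: reproduce the plan's figure.** With m = 4, lambda = 0.0625 × 84 × 4 / 0.5 = 42, df1 = 3 × 3 = 9 and df2 = 80 × 3 = 240. Power is 0.992. At N = 80 it is 0.988, so 84 is the smallest balanced total that reaches 0.99. Under sphericity, rho = 0.3 would have required 116 and rho = 0.7 would have required 52. This supports rho = 0.5 as the setting used.

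**Step 2: change only the number of measurements (N = 84, k = 4, rho = 0.5).**

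| Measurements | lambda | df | Power | Type II error |
|---|---|---|---|---|
| 4 (as stated) | 42 | 9, 240 | 0.992 | 0.8% |
| 3 (all scheduled fMRI visits) | 0.0625 × 84 × 3 / 0.5 = 31.5 | 6, 160 | 0.971 | 2.9% |
| 2 (before/after, as the primary outcome is defined) | 0.0625 × 84 × 2 / 0.5 = 21 | 3, 80 | 0.906 | 9.4% |

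**Step 3: vary the unstated correlation (N = 84, four-group interaction, epsilon = 1).**

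| rho | 4 measurements | 3 measurements | 2 measurements |
|---|---|---|---|
| 0.3 | 0.934 | 0.864 | 0.744 |
| 0.5 | 0.992 | 0.971 | 0.906 |
| 0.7 | >0.999 | >0.999 | 0.995 |

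Power of 0.99 at N = 84 is regained at rho of about 0.57 with three measurements and about 0.67 with two. The fall to 0.744 at rho = 0.3 is not all due to the visit count: the plan's own four-measurement test is already down to 0.934 there.

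**Step 4: a two-arm intervention-by-time test (k = 2, N = 84, rho = 0.5), taking f = 0.25 for that effect.** Before/after: lambda = 21, df 1 and 82, power 0.972. Three visits: lambda = 31.5, df 2 and 164, power 0.996.

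**The case against.** The case against giving this much weight has four parts.

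- **Rho is inferred.** Only 0.5 combined with sphericity has been matched to N = 84. A lower epsilon with a higher rho could also land near it: at epsilon = 0.75 the required total is 104 for rho = 0.5 and 64 for rho = 0.7. At a true rho of about 0.67 or more, the before/after test reaches 99% at N = 84. This stands, so the size of the shortfall is conditional. It does not rescue the stated calculation, which still counts a scan that is not made.
- **The size depends on the test.** The largest gap belongs to the four-group interaction. If the decisive term is intervention by time in two arms, before/after power is 0.972, under two points short. With all three scans it is 0.996, which exceeds the stated figure. This also stands. The article does not name the decisive term, so both sets of figures have to be shown.
- **The trial may still be adequately powered.** A reader might infer from the mismatch that the trial is underpowered or must recruit more. The documents do not support that: at the strict alpha of 0.01 and the inferred inputs, before/after power is above 90% for either test.
- **No patients-only test is stated.** A reader might want power within patients with MCI alone. The article plans no such primary test; all participants are analysed with diagnosis as a factor. Its f = 0.25 was set for the four-group design and cannot simply be carried to a subgroup.

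**Conclusion.** The sample size calculation contradicts the schedule and the definition of the primary outcome, and this can be seen without any assumption about rho. Follow-up 1 has no fMRI, hippocampal activity is measured three times at most, and the primary outcome uses two of those measurements. The stated 99% power is therefore not the power for the primary outcome.

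The size rests on assumptions. With rho = 0.5, sphericity, f = 0.25, alpha = 0.01 and N = 84, the four-group interaction has power of about 0.91 before/after (0.74 to 0.995 over rho 0.3 to 0.7) and 0.97 with three visits (0.86 to above 0.99). The two-arm test has 0.97 and 0.996 respectively at rho = 0.5.

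Severity is moderate. A figure on which the trial relies is wrong as written, but under the inputs that best reproduce it the power remains above 90%. It would go too far to say that the design fails to reach 99% whatever the correlation.

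**What to change.** Keep N = 84 and rewrite the sample size paragraph:

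1. Remove follow-up 1 from the fMRI calculation and set the number of measurements to those that enter the primary analysis, which is two for the before/after outcome as defined.
2. Name the interaction that the primary analysis tests: four-group by time, or intervention by time across two arms.
3. State the rho and epsilon used, with a short range for rho.
4. Restate the power. At rho = 0.5 it is about 0.91 for the four-group before/after interaction, or about 0.97 for the two-arm contrast.

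If the 12-month scan is meant to enter the primary ANOVA, the outcome definition in Statistical analyses should say so, and the three-visit figures then apply.

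The cost is one paragraph and a slightly less favourable stated power. No additional participants or visits are needed.

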### Data management

All data will be entered by the study team and stored using Research Electronic Data Capture (REDCap), hosted by the Clinical Trials Unit (CTU) Bern. The study team is responsible for data management; data monitoring will be done by an independent researcher not involved in the study. We will record any spontaneously reported adverse events or other unintended effects of the intervention. An annual safety report will be submitted once a year to the local Ethics Committee. Study data will be stored on servers of Bern University, stripped of personal information of the participants. Unblinding will occur after all raw data have been transferred to the data analysis software. All computers will be password-protected and encrypted. At the end of the study, all personal data will be deleted. The procedures comply with Swiss data privacy laws.

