**Methods:**

In a single-blind parallel-group study, we will randomize *n* = 84 individuals (*n* = 42 patients with MCI, *n* = 42 healthy elderly volunteers) to one of two groups receiving feedback from either the hippocampus or a functionally independent region. Percent signal change of the hemodynamic response within the respective target region will be displayed to the participant with a thermometer icon. We hypothesize that only feedback from the hippocampus will decrease hippocampal hyperactivity during pattern separation and thereby improve memory performance.

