## Background

Dementia due to Alzheimer’s disease (AD) is a neurodegenerative disorder associated with cognitive and functional decline. The underlying pathological process begins at least a decade before any clinical symptoms [1] and is characterized by neuronal cell death, extracellular deposits of amyloid-ß (Aβ) and intracellular formation of fibrillary aggregates of abnormally phosphorylated tau [2]. Activity in the hippocampus, as measured by functional magnetic resonance imaging (fMRI), is among the key emerging neuroimaging markers that allow an improved AD risk prediction [3]. In AD, hippocampal activity is typically decreased during memory tasks due to hippocampal atrophy. However, several fMRI studies in the prodromal stage of AD (i.e., in Mild Cognitive Impairment, MCI) have found increased hippocampal activity during memory tasks that was associated with memory deficits, subsequent cognitive decline and faster clinical progression [4–6]. Pattern separation, a process thought to critically depend on the hippocampus, has been particularly used as a task to show increased hippocampal activity in patients with MCI [7, 8]. Pharmacological treatment of hyperactivity in patients with MCI, or in mice with increased levels of Aβ, significantly reduced activity in the hippocampus and improved memory performance in pattern separation tasks [7]. Although one may expect that reducing brain activation in a given area will lead to a drop in performance, there is emerging evidence that hyperactivity in the hippocampus has a negative, rather than a positive, impact on cognition [9]. Thus, reducing excess hippocampal activity may present a promising therapeutic target. Pharmacological interventions, however, are prone to side effects such as headache, diarrhoea, or sleep disturbances. In addition, an elderly population is likely to be on other medication so - apart from the possible side effects - drug interaction may be a problem. An alternative approach may be real-time fMRI neurofeedback. With real-time fMRI neurofeedback, participants train to voluntarily ‘control’ region specific brain activity [10, 11]. The training is accomplished by continuously measuring brain activity in real-time, and providing feedback to the participant about the ongoing activity in the targeted brain area [11].

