## Methods

### Participants eligibility and recruitment

Eligible participants will be between 60 and 80 years of age, fluent in German, with normal or corrected-to-normal vision. Patients with MCI will be included if their memory performance is below age-, gender-, and education-adjusted norms as assessed with the delayed recall score of a list of words included in the CERAD neuropsychological battery (CERAD [12];). Other cognitive functions may also be below the norm but an impairment in memory performance is mandatory since this subgroup is particularly prone to hippocampal hyperactivity [7]. In addition, they will need to a) report a cognitive complaint, b) show no impairment in activities of daily living, c) show no dementia but d) show signs of neuronal injury (i.e., atrophy in the hippocampus or the medial temporal lobe) according to updated criteria [13]. This will provide intermediate certainty that MCI will develop into AD [13].

Healthy elderly participants will be included if their Montreal Cognitive Assessment (MoCA) score is ≥26 [12] and their Geriatric Depression Score (GDS) is ≤5 [14]. All participants will need to give written informed consent before the study. Exclusion criteria would be major psychiatric, neurological, or medical disorders or a history of epilepsy or severe head injury, current or life-time substance abuse, contra-indications to MRI, or psychoactive medication.

We will recruit healthy elderly volunteers via newspaper advertisements. Patients with MCI due to AD pathology will be recruited from the local memory clinic where they will receive their diagnosis. The study has been approved by the Ethics Committee of the Canton of Bern (2019–00958) and will be conducted in accordance with the declaration of Helsinki. Recruitment will continue until the required number of participants is reached.

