**Fig. 4 Fig4:**
[figure not shown]
Neurofeedback session. Each run will include four repetitions of baseline and regulation blocks, as well as the feedback presented using a thermometer icon. The thermometer icon will be filled with colours ranging from red to green during training or will remain grey during transfer. TR: Repetition time (1 TR = 2 s). The figure has been designed by the authors with stimuli illustrations from https://github.com/celstark/MST

Following the neurofeedback session, we will perform behavioural testing outside the scanner using a word list learning task (i.e., the VLMT [29];) that also probes memory functions. Afterwards, we will conduct debriefing of mental strategies. At the beginning and at the end of each session, we will apply the Profile of mood states (POMS [30];) and the Positive and Negative Affect Schedule (PANAS [31];) to assess whether the change in mood due to neurofeedback is similar for the control group and the experimental group.

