## Discussion

This study will examine whether real-time fMRI neurofeedback can reduce hippocampal hyperactivity and whether the reduction will lead to an improvement in memory performance. This will extend former research showing that a pharmacological reduction of excess hippocampal activity in patients with MCI led to better memory performance using a pattern separation task [7]. In contrast to medication, real-time fMRI neurofeedback comes with considerably fewer risks or side effects [33]. In addition, it may give patients a sense of empowerment as they themselves tone down hyperactivity without having to ‘depend on’ taking medication. So far, the assessment of the effectiveness of downregulating the hippocampus requires using a set-up including an MR scanner. This study may provide insight into strategies that participants have successfully used to regulate hippocampal activity. It would be such strategies that may be included in future cognitive intervention studies. Should our study be successful, we will test whether other participants could use such strategies for themselves or whether each person will need to develop their own strategy. In the context of clinical use, only a few training sessions may produce long lasting effects [34, 35].

One aspect that may likely influence our results is the type of control group [28]. We opted for an active control rather than no feedback or yoked feedback; that is, feedback is given on the activity of a control region. In our view, only the comparison with an active control group can confirm that the results are specific to feedback from hippocampal activity [16]. However, differences between groups might still be related to differences in the perceived difficulty to regulate. We will account for this by evaluating how difficult participants thought it was to regulate.

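### Adverse events are to be collected from spontaneous reports, with no standard enquiry described, in a sample half of which is selected for impaired memory

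*Protocol article*

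**What the plan says.** The Data management section of the protocol article has the only sentence on how adverse events are found: "We will record any spontaneously reported adverse events or other unintended effects of the intervention". The next sentence adds: "An annual safety report will be submitted once a year to the local Ethics Committee".

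Table 1 lists no adverse-event enquiry at any of the seven appointments, and no other section describes one. The contacts nearest to it, both in the Neurofeedback session section, are a debriefing on mental strategies after each training session and two mood scales (POMS and PANAS). The mood scales are given at the start and end of each training session "to assess whether the change in mood due to neurofeedback is similar for the control group and the experimental group".

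The abstract gives the MCI share of the 84 participants as "42 patients with MCI". The eligibility section says of these patients that "an impairment in memory performance is mandatory". Study procedure puts about a week between the early sessions and places the follow-ups 6 and 12 months after the post-intervention visit. The Discussion states that the investigators who prepare the regions of interest and the individual set-up will not be blinded.

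**The concern.** A spontaneous report reaches the record only if the participant notices the event, remembers it until the next contact and thinks it worth mentioning. The patients for whom the intervention is meant are chosen because their delayed recall is below the norm, and they would have to carry an event over a week or, later, over months. Capture is thus likely to be incomplete, and lower in MCI than in healthy participants. Complaints such as headache or poor sleep, and anything that happens between visits, are the most exposed, because no instrument in the schedule picks them up.

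Without a standard question, what is drawn out and written down also depends on the staff member. The Discussion treats separating those who prepare the set-up from those who instruct participants as a matter for future studies, so the person who hears a complaint may know the allocation.

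At stake is how a low or zero count can be read, both in the report to the Ethics Committee and in any table of events by arm or diagnosis. It would partly reflect how the events were collected.

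**Working it through.** **Inputs from the article.** Total 84 in four groups of 21 (Sample size calculation); 42 with MCI and 42 healthy (abstract, Methods). The planned hippocampal arm is therefore 21 MCI + 21 healthy = 42, and the MCI share of the sample is 42/84 = 50%.

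**Assumed inputs.** The article gives no capture rate. Let *c* be the share of events in MCI participants that become spontaneous reports, taken as 1, 0.50 or 0.25. Capture in healthy participants is set to 1, so that only the recall argument is at work. The true event rate *p* is taken as equal in both diagnostic groups, with at most one event counted per person.

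**Step 1: upper bound when no event is recorded in the arm.** The 95% upper bound is the *p* that solves (1 − p)^21 × (1 − c·p)^21 = 0.05, that is, (1 − p)(1 − c·p) = 0.05^(1/21) = 0.8671.

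- c = 1: p = 1 − 0.05^(1/42) = 0.069.
- c = 0.50: 0.5p² − 1.5p + 0.1329 = 0, so p = 0.091.
- c = 0.25: 0.25p² − 1.25p + 0.1329 = 0, so p = 0.109.

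**Step 2: chance of recording at least one case when the true rate is 5%.** This is 1 − 0.95^21 × (1 − 0.05c)^21, with 0.95^21 = 0.341.

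- c = 1: 1 − 0.95^42 = 0.88.
- c = 0.50: 1 − 0.341 × 0.975^21 = 1 − 0.341 × 0.588 = 0.80.
- c = 0.25: 1 − 0.341 × 0.9875^21 = 1 − 0.341 × 0.768 = 0.74.

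| Capture in MCI (assumed) | Upper bound, no events in 42 | Chance of at least one case, true rate 5% |
|---|---|---|
| 100% | 6.9% | 0.88 |
| 50% | 9.1% | 0.80 |
| 25% | 10.9% | 0.74 |

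**Step 3: what the schedule already captures without a volunteered report.** POMS and PANAS record mood at the start and end of both training sessions. The verbal learning test (VLMT) records memory at six of the seven visits in Table 1. Follow-up assessments repeats the cognitive screen (MoCA or CFD) at 12 months. Not covered are physical complaints, sleep, and events between visits.

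**The case against.** The strongest reply has five parts.

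- **The word 'only' is not in the article.** The sentence also covers other unintended effects, which can be read as wider than volunteered reports, and visit scripts are usually left to a full protocol. Table 1 is not exhaustive either: it omits the strategy debriefing and the repeat cognitive screen at 12 months. This stands as a caution. Still, the article names a passive method and gives no other way of finding unintended effects, so the point concerns a stated choice and not a missing detail.
- **Obvious harms are already measured.** Worsening of mood and of memory is captured by instrument in both arms, and staff see participants directly after each session. This stands, and it narrows the gap to physical complaints and events between visits.
- **The comparison between arms is largely protected.** Randomisation is stratified by diagnosis, so poorer reporting in MCI does not by itself bias that comparison. This stands. Uneven recording by unblinded staff is a separate route that stratification does not close.
- **These patients are not severely impaired.** They must have no dementia and no impairment in daily living, and an open question at 6 or 12 months relies on the same memory. Both are fair, and the second limits the remedy at the late visits.
- **There is no tolerability claim to undermine.** The Background says "Pharmacological interventions, however, are prone to side effects such as headache, diarrhoea, or sleep disturbances", and the Discussion says "In contrast to medication, real-time fMRI neurofeedback comes with considerably fewer risks or side effects". A reader might infer that the trial means to show fewer side effects than drugs and that spontaneous reporting defeats this aim. The article does not support that. The Discussion's statement is background resting on a cited source, neither the stated aims nor the statistical analyses name safety, and with no drug arm no method of collecting events could test the comparison.

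A reader might also apply reduced capture to all 42 participants in the hippocampal arm. That gives upper bounds of 13.8% (6.9%/0.5) and 27.5% (6.88%/0.25), but it treats the 21 healthy volunteers as if they too were selected for poor memory.

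**Conclusion.** The concern holds as a minor point of design. The article fixes a passive method for adverse events in a sample half of which must have impaired memory, and describes no standard enquiry. The likely result is under-counting, more so in MCI, with some room for uneven recording by staff who know the allocation. It touches the adverse-event counts, their comparison between MCI and healthy participants, and the annual safety report. It does not touch the primary analysis.

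The size is modest: under the assumptions above, the bound after zero events moves by about 2 to 4 percentage points (6.9% to 9.1% or 10.9%), and the chance of detecting an event with a 5% rate falls by about 0.08 to 0.14. These figures rest on capture rates that the article does not give and on full capture in healthy participants, which is itself optimistic. They show the direction and rough scale and are not an estimate of what the trial will miss.

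**What to change.** In Data management, keep the recording of spontaneous reports and add the following: every participant in both arms is asked the same scripted open question on new or worsened complaints after each of the two neurofeedback sessions, at the post-intervention visit and at both follow-ups. The answers are logged in REDCap, solicited and volunteered events are marked as such, and events are tabulated by arm and by diagnosis.

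The cost is about a minute at five visits that already take place, plus one REDCap form. The downside is a longer list of minor events. Recall at the 6- and 12-month visits stays limited even with a question, so events reported there should be read with caution.
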